#### Strengthening the brain

‘Strengthening the brain’ is a lifestyle intervention which combines physical exercise with cognitive training.

For the exercise component, participants receive exercise and lifestyle coaching (part in kind contribution of Personal Fitness Nederland, Fit for Life programme, www.personalfitnessnederland.nl) where one-on-one training will be provided at one of the 94 studios of Personal Fitness Nederland (PFN). Every session will exist of a combination of cardio (aerobic) and strength (anaerobic) training dependent on the goals of the participant. At the start of the programme an intake will take place, where the physical fitness of the participant will be determined, and attention will be paid to specific health issues and goals of the participant. Sessions will be made increasingly more challenging. Each session will start with weighing the participant followed by 30 min of exercise in a studio where no other people are present, guaranteeing full attention to the participant. Next to the weekly face-to-face sessions, participants are asked to perform pre-set exercises at home twice a week (20 min each) which are guided by instruction videos on an online platform. A quantitative assessment of the adherence (how many sessions attended and progress between training sessions) will be done by the lifestyle coach and participants will write down their goals concerning exercise and diet for the upcoming week in a personal log. Lifestyle coaches will also provide participants with diet schemes and mental coaching. This will also be recorded using the personal log.

For the cognitive component, participants will follow cognitive training using a Dutch home-based computerised cognitive training, BrainGymmer^©^ (https://www.Braingymmer.com), which has been used in multiple studies [34–37]. A variety of cognitive functions are trained (information processing speed, spatial memory, working memory, executive functioning) rather than one cognitive function in particular. The cognitive training will focus on the cognitive function that was most impaired on the neuropsychological assessment at baseline. The training has an adaptive mechanism, which will adjust to the participant’s performance level to make it challenging for all participants. The programme will log training time and the percentage of correctly performed games. Participants are instructed to train for 60 min per week.

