#### Strengthening the mind

The ‘strengthening the mind’ intervention consists of biweekly contact with trained work coaches who are all diagnosed with MS themselves (in kind contribution of the Dutch MS Society, MSVN). The intervention focuses on (re)discovery of a sustainable and healthy balance between relevant work values, the challenges workers with MS are facing, and at the same time meeting the work demands in a dynamic work context with ongoing technological developments. This will be reached using a combination of the capability approach and the participatory approach: “Working Positively”. The starting point of the capability approach related to work participation is to explore what people find important and valuable in work – what they would like to achieve in a given (work) context – and moreover, in the case of individuals confronted with a chronic and progressive disease such as MS, to ascertain whether people are enabled and able to do so. The participatory approach uses a practical, stepwise manner to detect challenges at the workplace and implement solutions by actively involving both the worker and the workplace (e.g., the supervisor).

Every participant will be matched with a trained work coach that also has an MS diagnosis. The starting point (step 1) of the coaching will be an assessment of individual work values using the capability set for work questionnaire [38] and to become acquainted with the worker and their working context. This starts by identifying which work values are important to the worker with MS. Secondly, it will be assessed to what extent workers are enabled to achieve these values at work, and thirdly to what extent they are able to achieve these values at work. Any discrepancies patients experience in being enabled and able to achieve important work values will be flagged, as these indicate barriers for optimal and satisfactory work participation [39]. Additionally, the employer or other representative of the workplace will be requested to join at least one coaching session to provide information related to work demands and context from their perspective as is described as an essential element of the participatory approach. In case the participant prefers not to disclose their MS diagnosis to the workplace, an independent occupational health professional may act as a representative of the workplace.

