#### Enhanced usual care

Participants in the enhanced usual care condition will watch a pre-recorded video together with a researcher with the opportunity to ask questions afterwards. The video provides a standardised explanation of cognitive decline in PwMS based on the Dutch book “MS and Cognition, by scientists for people with MS and their surroundings” (editors: [name] & [name]). The video includes information about the frequently affected cognitive domains in MS and their relation to brain pathology. Participants will be asked to continue their life ‘as is’ during the time of the intervention (4 months). The main reason for incorporating enhanced usual care in the protocol is to avoid resentful demoralisation of participants assigned to this group.

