### Work Package 3: Qualitative study

A selection of stakeholders involved in the project (PwMS, lifestyle- and work coaches, neurologists, neuropsychologists, occupational physicians, and occupational therapists) will be invited for the semi-structured interviews and focus groups. The interviews aim to provide insight into the experiences of stakeholders regarding the interventions and will be planned in batches to ensure an equal number of participating patients and coaches during the whole study period, preferably within a timeframe of 3 months from the last training session to avoid recall-bias. Interviews will be based on a topic list to ensure that all relevant questions will be addressed, and will continue until saturation is reached, meaning that no new themes emerge from the analysis. In case logistical improvements are brought up during the early interviews, adjustments will be made for future participants (e.g., if participants prefer to exercise in the morning rather than in the evening). Content-wise no changes will be allowed to the interventions. It is expected that 12–15 interviews with participants and 10–12 interviews with professionals from each group will be sufficient to reach saturation. Focus groups will be organised to further understand the effects of the ‘strengthening the brain’ and ‘strengthening the mind’ interventions, and to explore factors that promote or hinder the implementation of the interventions. The focus groups will consist of 8–10 participants to ensure optimal exchange of perspectives and dialogue and a script will be prepared. First, we will organize homogeneous focus groups (with participants and professionals separately); next, a heterogeneous dialogue group will be held in which participants and professionals reflect on the experiences and outcomes together. In forming focus groups, we will include diverse participants (considering sex, age, educational level). Focus groups will be organised after the individual interviews have been conducted and analysed, and short-term quantitative measures have been assessed.

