### Sample size

The sample size of 270 participants is based on a power calculation. A review of earlier studies on the effects of cognitive rehabilitation in MS [14] suggests that we can expect moderate effects (effect size of 0.35) between pre- and post-intervention. Assuming statistical significance of 0.025, a power of 0.80, and an effect size of 0.35, 75 participants per group are needed. A conservative alpha of 0.025 has been chosen to take into account that we compare two interventions with a control group. A correlation of 0.6 between the measures was assumed. Based on previous experiences, a drop-out of 20% over the study period is expected. Therefore, we will include 90 subjects per group to ensure sufficient power. This study will be carried out using an intention-to-treat protocol. Therefore, subjects who withdraw from the study after inclusion will not be replaced.

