Primary analyses will evaluate the effectiveness of the investigated interventions (‘strengthening the brain’, ‘strengthening the mind’) compared to a control group (‘enhanced usual care’) in improving HRQoL (overall score on SF-36). A mixed-model analysis will be performed, with time (T0, T1, T2, and T3) and condition (‘strengthening the brain’, ‘strengthening the mind’, and ‘enhanced usual care’) as fixed factors, and subject as random factor. P-values and estimates of effect sizes will be obtained. Additionally, separate mixed-model analyses will be performed to evaluate the effect of the investigated interventions compared to the control group on cognitive, psychological, physiological, and work functioning, and enhancing the brain’s functional network. Predictors of treatment response will be investigated by adding baseline scores on the biological, psychological, and environmental measures to the mixed-model analyses.

Mediation analyses will be used to study which mechanisms (i.e.., biological, psychological, and environmental) mediate the effect of the interventions on HRQoL. Conditions for mediation will be tested [104]: 1) investigated interventions should affect HRQoL; 2) investigated interventions should affect the presumed mediator; 3) presumed mediator and HRQoL should be related.

The cost-effectiveness analyses will be performed from a healthcare and a societal perspective according to the intention-to-treat principle. Intervention costs will be calculated using a bottom-up micro-costing approach. Missing cost and effect data will be imputed using multiple imputation by chained equations (MICE) with predictive mean matching to account for the skewed distribution of costs. The number of imputed datasets will be increased until the loss of efficiency is smaller than 5% [105]. Each dataset will be analysed separately as described below, after which results will be pooled using Rubin’s rules. Bivariate regression models will be used to estimate cost and effect differences between the intervention groups and the control group, while adjusting for confounders if necessary. Incremental cost-effectiveness ratios will be calculated by dividing the difference in costs by the difference in effects. Statistical uncertainty will be estimated using bias-corrected and accelerated bootstrapping and will be presented in cost-effectiveness planes and acceptability curves. Sensitivity analyses are performed to assess the robustness of the results.

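### Coaches deliver two of the three arms, but the primary model has no coach term; if coaches are shared, the standard error against control is too small, mainly for 'strengthening the mind'

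*Protocol article*

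**What the plan says.** In the protocol article, Statistical analysis, the primary model for the overall SF-36 score has time (T0 to T3) and condition (three arms) "as fixed factors, and subject as random factor". No coach or studio term appears in that section, and Sample size makes no allowance for clustering.

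Delivery differs by arm:

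- **Strengthening the mind:** "Every participant will be matched with a trained work coach that also has an MS diagnosis". Contact is biweekly for up to four months, and the coaches are an in-kind contribution of one patient society.
- **Strengthening the brain:** "one-on-one training will be provided at one of the 94 studios of Personal Fitness Nederland".
- **Enhanced usual care:** participants "will watch a pre-recorded video together with a researcher with the opportunity to ask questions afterwards". There is no coach.

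The article does not say how many coaches there are, how many participants each takes, or whether coaches are shared.

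**The concern.** Participants are randomised individually, but two of the three arms are then delivered by particular people. This is a partially nested design: participants can be grouped by coach in the intervention arms, while each control stands alone. A subject random effect accounts for repeated measures within one person. It cannot account for similarity between different people who had the same coach.

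If such similarity exists and is ignored, intervals and p-values for the intervention contrasts are too optimistic, and the work of a few good or poor coaches can be read as an effect of the method. The error goes in one direction, and it erodes the 0.025 level that Sample size sets for comparing two interventions with one control.

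**Working it through.** **Inputs from the article.** Sample size: "Assuming statistical significance of 0.025, a power of 0.80, and an effect size of 0.35, 75 participants per group are needed"; correlation 0.6; 90 randomised per group. Strengthening the brain: 94 studios. Sidedness is not stated; two-sided is taken here.

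**Inputs assumed.** Caseload m and coach ICC. The ICC that matters is the one for the treatment contrast, that is, for change in SF-36.

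**1. The plan's own figure.** The two-group formula gives 2 × (2.241 + 0.842)² / 0.35² = 155.2, so 156 per group. Baseline adjustment, × (1 − 0.6²), gives 100. A change score, × 2(1 − 0.6), gives 125. None of these gives 75. That is a separate matter. Below, 80% power at 75 per group is taken at face value, only as the point from which a loss is measured.

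**2. Formulas.** Design effect in the coached arm: DE = 1 + (m − 1) × ICC. Controls have DE = 1, so the contrast variance is multiplied by (1 + DE)/2, and true SE / model SE = R = √((1 + DE)/2). Real error at nominal 2.5% is 2(1 − Φ(2.241/R)). Power of a test that uses the correct SE is Φ(3.083/R − 2.241), where 3.083 = 2.241 + 0.842.

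**3. Worked case.** With m = 9 and ICC = 0.05: DE = 1.40; variance factor 1.20; R = 1.095; real error 2(1 − Φ(2.241/1.095)) = 4.1%; power Φ(3.083/1.095 − 2.241) = 0.72.

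**4. Range.** For illustration, 10 to 12 coaches would give m = 75/12 = 6.25 up to 90/10 = 9. The rows for 1, 3 and 15 show what happens outside that range. Cells are for ICC 0.02 / 0.05 / 0.10.

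| m | R | Real error, % | Power, % |
|---|---|---|---|
| 1 | 1 / 1 / 1 | 2.5 / 2.5 / 2.5 | 80 / 80 / 80 |
| 3 | 1.010 / 1.025 / 1.049 | 2.65 / 2.87 / 3.26 | 79 / 78 / 76 |
| 6.25 | 1.026 / 1.064 / 1.124 | 2.89 / 3.51 / 4.61 | 78 / 74 / 69 |
| 7.5 | 1.032 / 1.078 / 1.151 | 2.99 / 3.76 / 5.15 | 77 / 73 / 67 |
| 9 | 1.039 / 1.095 / 1.183 | 3.10 / 4.07 / 5.82 | 77 / 72 / 64 |
| 15 | 1.068 / 1.162 / 1.304 | 3.58 / 5.37 / 8.56 | 74 / 66 / 55 |

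**5. 'Strengthening the brain'.** If participants spread evenly at random over 94 studios, each has on average (75 − 1)/94 = 0.79 to (90 − 1)/94 = 0.95 studio-mates. Putting this in place of m − 1 gives R = 1.004 to 1.012 for ICC 0.02 to 0.05, and at most 1.023 at ICC 0.10. The effect is larger only if participants concentrate in a few studios.

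**6. Where the term must act.** T0 is one of the modelled outcome times and is measured before randomisation, so the treatment effect lies in the condition-by-time contrast. Write c for a coach's effect. If c enters equally at T0, T1, T2 and T3, it drops out of every change from T0 and cannot widen that contrast's SE. If c enters only at T1 to T3, which is when coaching can act, it stays in the change and adds its variance divided by the number of coaches to the variance of the arm mean.

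**The case against.** The strongest objection is that sharing of coaches is never stated. A reader might infer that participants in both arms do share coaches and that the standard errors are therefore too small. The article does not support that as fact: with one participant per coach the inflation is zero at any ICC. A reader might also take "10–12 interviews with professionals from each group will be sufficient to reach saturation" as the number of coaches. It is an expected saturation figure for the qualitative study. If 10 to 12 different work coaches were interviewed, at least that many would exist, so 9 per coach would be an upper bound. Nor does the text describe the work coaches as volunteers or as a limited pool.

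These points make the claim conditional but do not remove it. One coach per participant would need about 90 trained work coaches who have MS, all supplied through one society, which is implausible. The objection does hold for 'strengthening the brain', where the inflation may be about 1% or less.

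It can also be said that a condensed article leaves random-effects detail to the full protocol or SAP, and that a coach effect matters mainly when generalising to other coaches. The first is fair for covariance structure, but here the article does name the random factor, and names only one. On the second, the stated aim of introducing the interventions into clinical practice implies other coaches.

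Finally, the 80% anchor could not be reproduced and every ICC is assumed. The power figures therefore show relative loss and do not forecast the trial's power.

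**Conclusion.** The point holds in conditional form. The stated model leaves out a source of correlation that the design makes possible in two arms and likely in one. If work coaches take about 6 to 9 participants each and the coach ICC is 0.02 to 0.10 (both assumed), the true SE for 'strengthening the mind' versus control is about 3 to 18% above the model's. Real error at nominal 2.5% is then about 3 to 6%, and power falls from 80% to about 64 to 78%. With caseloads near one, nothing changes. The documents do not support a statement that the standard errors are wrong in both arms. The change is still worth making, because it is cheap and the possible error favours the interventions.

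**What to change.** State the number of coaches and their caseloads, and record a coach identifier for every participant in the two intervention arms. Coaches are already told of each inclusion and already log contacts or attendance, so this should be available. In the primary model, add a coach random effect in the intervention arms only, acting on T1 to T3 (a coach-by-post-baseline term), with each control as its own cluster. Use small-sample degrees of freedom and report the coach ICC. A coach intercept constant over T0 to T3 is not enough.

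Costs: one more field in the database, one more model term and slightly wider intervals. Small-sample degrees of freedom may widen the interval a little even if the coach variance is estimated as zero. There is also a blinding cost: under Allocation and blinding the analysts are not told the allocation, and clusters in two arms with singletons in the third could reveal the control arm. Coach identity should therefore be coded, held apart and merged only at the final analysis. Recruitment was still under way when the article was written; the term should be specified before the allocation is revealed to the analysts.

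### The 5% efficiency rule for the number of imputed datasets leaves the economic results, above all the acceptability curves, dependent on the random seed

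*Protocol article*

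**What the plan says.** All of the following is in the protocol article.

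- **Imputation (Statistical analysis).** "Missing cost and effect data will be imputed using multiple imputation by chained equations (MICE) with predictive mean matching", the last part being chosen because costs are skewed.
- **Number of datasets (same section).** "The number of imputed datasets will be increased until the loss of efficiency is smaller than 5" per cent. A reference is cited. The paragraph gives no minimum number and no criterion based on Monte Carlo error.
- **Pooling (same section).** "Each dataset will be analysed separately as described below, after which results will be pooled" by Rubin's rules. Each intervention is compared with control, from a healthcare and a societal perspective.
- **Outputs (same section).** Incremental cost-effectiveness ratios are calculated. Their uncertainty is bootstrapped, and the results "will be presented in cost-effectiveness planes and acceptability curves".
- **Robustness (same section).** "Sensitivity analyses are performed to assess the robustness of the results". What these analyses contain is not stated.
- **Missing data (Sample size).** The only figure in the document is that "a drop-out of 20% over the study period is expected". No FMI is given.

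**The concern.** Multiple imputation with a finite number of datasets, m, adds random noise to every pooled result. A limit on efficiency loss asks one question: how much larger is the variance of the pooled estimate than with infinitely many datasets? Few datasets are enough to pass that test.

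A different question matters for a published economic evaluation: would the same data, imputed again with another seed, give the same numbers? The 5% rule does not address it. The exposed outputs are p-values, cost-effectiveness ratios (noise in both numerator and denominator) and, most visibly, the acceptability curve, where a modest shift in net benefit moves the reported probability a long way. Cost-effectiveness is the fourth secondary aim of the trial, and these are the figures that readers would use when deciding on adoption.

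**Working it through.** **Inputs.** From the document: the 5% limit, pooling by Rubin's rules, two interventions against control, and two cost perspectives. Assumed: an FMI of 0.2 to 0.5. The expected 20% drop-out is not itself an FMI; it only suggests the order of magnitude. The document states no number of datasets, so there is no figure of its own to reproduce.

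**Step 1: where the rule stops for one difference.** With relative efficiency 1/(1 + FMI/m), the loss is FMI/(m + FMI). The smallest m with a loss below 0.05, and the Monte Carlo SD of the pooled estimate in units of its SE, √(FMI/m), are:

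| FMI | smallest m | loss | Monte Carlo SD / SE |
|---|---|---|---|
| 0.2 | 4 | 0.2/4.2 = 0.048 | √(0.2/4) = 0.224 |
| 0.3 | 6 | 0.3/6.3 = 0.048 | √(0.3/6) = 0.224 |
| 0.4 | 8 | 0.4/8.4 = 0.048 | √(0.4/8) = 0.224 |
| 0.5 | 10 | 0.5/10.5 = 0.048 | √(0.5/10) = 0.224 |

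For FMI 0.1 and 0.6 the smallest m is 2 and 12. The last column does not change, because stopping at the limit sets FMI/m to 0.05. For the difference that governs stopping, the noise is therefore about 0.22 SE whatever its FMI.

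**Step 2: if several differences must meet the rule.** Healthcare cost, societal cost and one effect, for two comparisons, make 3 × 2 = 6 differences. I simulated adding datasets until all six estimated losses were below 5%, with independent imputation noise assumed and a start at 2, 3 or 5 datasets.

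- All six with FMI 0.3: mean m about 9, Monte Carlo SD about 0.19 SE.
- FMIs mixed from 0.2 to 0.5: mean m about 10.4. The Monte Carlo SD was about 0.14 SE at FMI 0.2, 0.17 at 0.3, 0.20 at 0.4 and 0.22 at 0.5. Direct arithmetic at m = 10 agrees: √(0.2/10) = 0.14, √(0.3/10) = 0.17, √(0.4/10) = 0.20, √(0.5/10) = 0.22.

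**Step 3: effect on the acceptability curve.** Take a probability of cost-effectiveness of 0.80, so z = 0.842, with a normal approximation and the SE held fixed. The central 95% of seeds is Φ(0.842 ± 1.96 × Monte Carlo SD).

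- 5% rule, governing comparison: Φ(0.842 ± 1.96 × 0.224) = Φ(0.403) to Φ(1.281) = 0.66 to 0.90.
- m = 100, FMI 0.3: Monte Carlo SD = √(0.3/100) = 0.055, giving Φ(0.735) to Φ(0.949) = 0.77 to 0.83.

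A simulation that also lets the pooled SE vary between seeds gives about 0.65 to 0.91 under the 5% rule.

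**Step 4: effect on a p-value.** Take a difference whose z would be 2.1 with infinitely many datasets (p about 0.036). Over 100,000 simulated re-imputations, with 147 complete-data degrees of freedom assumed and FMI 0.2 to 0.4, p falls below 0.05 for 53% to 57% of seeds at the m of the 5% rule. At m = 100 the share is 89% to 98%.

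**Step 5: interval coverage under sequential stopping.** With one difference at FMI 0.3 governing the rule and a start at 2 to 5 datasets, simulated coverage of nominal 95% intervals is about 0.92 to 0.95. When all six differences must meet the rule, it is about 0.95.

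**The case against.** The strongest case for the plan has four parts.

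- **The rule is prespecified and coherent.** It adapts to the missing information observed, and a reference is cited. It sets where the team may stop and does not forbid more datasets. This stands, and for that reason the point is an improvement to a stated rule and not the correction of an error. The text gives no reason to go beyond the limit, however.
- **Finite-m noise is already in the interval.** Rubin's rules add the between-imputation variance divided by m. At the limit the variance rises by a factor of 1.05, so the SE rises by a factor of √1.05 = 1.025. This stands too. The problem is reproducibility, not validity.
- **The noise is not the same for every difference.** A reader might infer from Step 1 that each pooled difference carries about 0.2 SE. If the rule has to hold for all differences, only the one with the highest FMI does, and the others carry less.
- **Seeds, minimum numbers and error reports are commonly left to an analysis plan.** That is fair for those details, and their absence is not the finding. The stopping criterion itself is stated in the article, so it can be judged.

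A reader might also infer that stopping at the first low estimate makes the intervals too narrow. The document does not support this. Undercoverage appears only if a single difference governs stopping from a low starting number, and the text specifies neither. It vanishes when the six differences must all meet the rule.

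**Conclusion.** The point holds as a minor one. With an assumed FMI of 0.2 to 0.5, the 5% rule is met at about 4 to 10 datasets for a single difference, or about 9 to 11 on average if all six must meet it (FMI 0.3 throughout, or a mix of 0.2 to 0.5). The m values depend on that assumption; the noise of about 0.2 SE for the governing difference does not. The range of 0.66 to 0.90 applies to that comparison, at a probability of 0.80 and under a normal approximation. Comparisons with a lower FMI move less.

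The rule does what it claims for the efficiency of the point estimate. It is not enough to make p-values, cost-effectiveness ratios or acceptability curves reproducible. Nothing here touches the primary analysis of the SF-36, which lies outside the paragraph that sets this rule.

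**What to change.** Replace the 5% rule in the economic analysis by one of these:

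1. A larger number fixed in advance, for example m = 100.
2. Adding datasets until the Monte Carlo error of each cost and effect difference is below 0.1 SE and that of the probability of cost-effectiveness is below 0.02, and reporting that error.

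The first part of option 2 alone needs FMI/m < 0.01, that is m above 100 × FMI, or 20 to 50 for FMI 0.2 to 0.5. The second part is stricter. At a probability of 0.80 the normal density is 0.280, so m = 100 with FMI 0.3 gives an error of 0.280 × 0.055 = 0.015. At a probability of 0.50 the density is 0.399 and the error is 0.022, so slightly more than 100 datasets would be needed there.

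The cost is one line in the analysis plan and extra computing time, since more imputed datasets have to be bootstrapped. No new data are needed.

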### Outcome measures

#### Work package 2: Randomized controlled trial

As illustrated in Figs. 1 and 2, measurements in the randomized controlled trial will take place right before the intervention (baseline; T0), directly after the intervention (four months after baseline; T1), at short- and long-term follow-up (10 months (T2) and 16 months (T3), respectively).

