##### Societal costs and general quality of life

Societal costs include healthcare, patient and family, and lost productivity costs and will be assessed using the iMTA Productivity Cost Questionnaire (iPCQ) [87] and iMTA Medical Cost Questionnaire (iMCQ) [88]. Additionally, the EuroQol five-level questionnaire (EQ-5D-5L) will be used to measure general quality of life. The Dutch EQ-5D-5L tariff will be used to convert EQ-5D-5L health states to utility scores to enable the calculation of quality-adjusted life-years (QALYs) [89, 90].

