### Allocation and blinding

After baseline measurements, participants will be randomly assigned to one of the three conditions with a 1:1:1 allocation using a block randomisation of Research Randomizer (https://www.randomizer.org) to ensure equal group sizes. The block randomisation will not be disclosed to researchers performing measurements and analyses. After receiving informed consent, the involved lifestyle coach or work coach will be informed of the inclusion of the participant in their treatment arm by a researcher who is not involved with the measurements and analyses. Cognitive measures, structural and functional brain measures, neurological-, blood-, and physiological measures will be collected, analysed, and stored under a single-blinded protocol. To achieve single blinding, eligible participants will be randomised and assigned to an intervention by three designated researchers ([name]) who are not involved in data collection and analyses. The researchers who are involved in data collection and analyses ([name]) are not informed about the allocation, nor discuss the intervention with the participants and involved coaches. In addition, researchers who carry out the measurements will explicitly instruct participants not to disclose any information about the intervention they are following.

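### Adjustment in the economic evaluation is left to 'if necessary'; baseline utility should always be in the QALY equation, and baseline costs in the cost equation where they are collected

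*Protocol article*

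**What the plan says.** In the protocol article, the cost-effectiveness paragraph of the Statistical analysis section uses bivariate regression for the cost and effect differences between each intervention and control, "while adjusting for confounders if necessary". It names no covariate and does not say how necessity is judged. The same paragraph is specific elsewhere: chained-equation imputation with predictive mean matching, a 5% limit on efficiency loss, Rubin's rules, and bias-corrected and accelerated bootstrapping.

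The section Societal costs and general quality of life converts EQ-5D-5L states to utilities with the Dutch tariff, "to enable the calculation of quality-adjusted life-years (QALYs"). It takes costs from the iPCQ and iMCQ but gives no time points for any of the three instruments. The Outcome measures section places trial visits at baseline and at 4, 10 and 16 months. Allocation and blinding states that participants are randomised after baseline measurements, "with a 1:1:1 allocation using a block randomisation"; no stratification factor is stated.

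**The concern.** Confounding is a concept for non-randomised comparisons. Here baseline utility is measured before allocation and groups differ on it only by chance, so no property of the design can make adjustment necessary or unnecessary. In practice necessity would probably be judged from the observed baseline table, which makes the model depend on the data.

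Baseline utility also matters more to QALYs than an ordinary covariate does. If QALYs are an area under the utility curve from T0, baseline utility is part of the outcome and also predicts every later utility. Adjusting for it pays whether or not an imbalance is seen.

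The QALY difference is the denominator of an ICER, and its uncertainty shapes the cost-effectiveness planes and acceptability curves. Both interventions are compared with the same control arm, so a chance imbalance in that arm enters both comparisons.

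**Working it through.** The article gives no standard deviation, power or expected difference for the economic evaluation, so there is no stated figure to reproduce. What follows only sizes the effect.

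**Inputs from the article**
- Visits at 0, 4, 10 and 16 months (Outcome measures).
- 90 participants per arm (Sample size).
- "A correlation of 0.6 between the measures was assumed" (Sample size). This is stated for the power calculation, not for utilities.

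**Assumptions**
- QALYs by the trapezoidal rule.
- The same correlation ρ between all pairs of visits: 0.6 borrowed, range 0.4 to 0.8.
- The same utility SD at every visit: 0.20, range 0.15 to 0.25.

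**Weights.** The trapezoidal rule gives T0 4/2 = 2 months, T1 (4+6)/2 = 5, T2 (6+6)/2 = 6 and T3 6/2 = 3. In years, w = (0.167, 0.417, 0.500, 0.250).

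**Variance of the QALY at ρ = 0.6**, in units of the utility variance:
- Σw² = (4+25+36+9)/144 = 0.514, and (Σw)² = (16/12)² = 1.778.
- Var(QALY) = (1−ρ)Σw² + ρ(Σw)² = 0.4 × 0.514 + 0.6 × 1.778 = 1.272.
- Cov(QALY, T0) = 0.167 + 0.6 × 1.167 = 0.867. This is also the slope of QALY on baseline utility.
- Residual variance after adjustment = 1.272 − 0.867² = 0.521.
- Variance ratio = 0.521/1.272 = 0.41, so the SE ratio = √0.41 = 0.64.

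**Over the range of ρ.** These ratios do not depend on the utility SD or the number per arm.

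| ρ | slope | variance ratio | SE ratio |
|---|---|---|---|
| 0.4 | 0.633 | 0.607 | 0.78 |
| 0.5 | 0.750 | 0.509 | 0.71 |
| 0.6 | 0.867 | 0.410 | 0.64 |
| 0.7 | 0.983 | 0.309 | 0.56 |
| 0.8 | 1.100 | 0.207 | 0.45 |

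**Size of a chance imbalance.** With SD 0.20 and 90 per arm, one standard error of the baseline difference is 0.20 × √(2/90) = 0.030 utility. Unadjusted, it moves the QALY difference by 0.867 × 0.0298 = 0.026 (0.019 to 0.033 for ρ from 0.4 to 0.8). At ρ = 0.6, with SD from 0.15 to 0.25, the move is 0.019 to 0.032.

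**Three rules compared.** In 20,000 simulated two-arm comparisons (90 per arm, SD 0.20, ρ = 0.6), the SE of the QALY difference was:
- never adjusting: 0.0336;
- adjusting only when the baseline difference has p<0.05: 0.0307;
- always adjusting: 0.0215.

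The conditional rule recovers (0.0336 − 0.0307)/(0.0336 − 0.0215) = 0.0029/0.0121, about a quarter of the gain. Under randomisation the test triggers in only about 5% of trials, so the other 95% go unadjusted.

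**Costs.** The SE ratio is √(1−r²), where r is the correlation of baseline with follow-up costs. Assumed values of 0.3, 0.5 and 0.7 give 95%, 87% and 71%. The article gives no such correlation.

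**The case against.** The strongest reply is that this is a journal article. The sentence allows baseline adjustment, a bivariate regression readily takes covariates, and the covariate list may stand in the full protocol or an analysis plan that is not shown. *If necessary* could also be settled in advance, since the article mentions no significance test. This limits the claim: the loss is something the wording permits, not something it dictates. It does not remove the point, because the article states a condition for adjusting, and a plan that always adjusted would replace that condition.

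Three stronger readings are tempting, and the article does not support them.

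- **That the unadjusted result is biased.** Under 1:1:1 randomisation it is unbiased on average. A one-standard-error imbalance moves the QALY difference by 0.026, less than the unadjusted SE of 0.0336, and the planned bootstrap would reflect that sampling variation. The cost is lost precision and imbalance in the realised sample.
- **That both baseline covariates are already in hand.** T0 utility is a fair inference from the visit schedule and the use of EQ-5D-5L for QALYs. Collection of costs at T0 is not established: the text gives no time points for the cost questionnaires, and the figure with the schedule is not shown.
- **That 0.6 is the trial's own correlation for utilities.** It belongs to a sample size built on a pre-to-post effect. Its use here, like the trapezoidal rule, is an assumption.

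Analyst discretion is also partly restrained. Allocation and blinding keeps researchers involved in the analyses unaware of allocation, although its list of blinded measures does not name utilities or costs.

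**Conclusion.** The point holds as a weakness in a stated rule. Conditional adjustment has no fixed target in a randomised comparison, and a plainly better rule is available. Under the assumptions above, always including baseline utility reduces the SE of the QALY difference to about 64% of the unadjusted value, with a range of 78% to 45%. A trigger at p<0.05 would forgo about three quarters of that gain. The direction does not depend on the exact correlation; the size does.

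For costs the case is conditional. It needs baseline costs to have been collected, and the gain is small if they correlate weakly with later costs.

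The change is worth making but its reach is limited. Cost-effectiveness is the fourth secondary aim, and the primary SF-36 analysis is not affected.

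**What to change.** In the cost-effectiveness paragraph of the Statistical analysis section, replace the phrase about confounders with: *The QALY equation always includes baseline EQ-5D-5L utility, and the cost equation includes baseline costs where these are collected; any further covariates are fixed before unblinding.*

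This costs one sentence and, provided EQ-5D-5L is given at T0, needs no new data. The article reports that recruitment was still under way, so at that stage the rule could be settled before any analysis. The sponsor should check the assessment schedule to see whether the cost questionnaires are given at T0, and word the cost part accordingly.
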